### Exclusion criteria

Multiple colorectal cancers or multiple other primary malignancies (concurrent multiple cancers with a disease-free interval of ≤ 5 years at the time of registration). However, lesions equivalent to intraepithelial or intramucosal carcinomas, which are considered curable with local treatment, will not be considered as multiple cancers.Ulcerative colitis-related cancers.Cases in which patients request to withdraw from participation in this study.Cases deemed inappropriate by the investigator.

### Endpoints

The primary endpoint is the incidence of postoperative complications (Clavien–Dindo classification grade ≥ III) [35]. The rate of severe postoperative complications in all eligible patients will be investigated, and risk factors affecting them will be determined.

A key secondary endpoint is the incidence of intraoperative vascular injury around the SMV. The rate of intraoperative vascular injury around the surgical trunk in all eligible patients will be investigated, and risk factors affecting it will be extracted.

Other secondary endpoints include the incidence of postoperative complications (Clavien–Dindo classification grade ≥ II), 5-year overall survival, recurrence-free survival, and other short- and long-term outcomes (operative time, blood loss, conversion rate, degree of lymph node dissection, intraoperative complication rate, reoperation rate, R0 resection rate, local recurrence rate in the whole cohort and by stage, and incidence of bowel obstruction and herniated abdominal wall scarring). Factors influencing the above endpoints will be determined for all eligible patients. Furthermore, comparisons will be made between each subgroup, as shown in Table 1.

**Table 1 Tab1:** Secondary endpoints

1. Short-term results by approach (a. Medial approach vs. retroperitoneal approach; b. Medial approach vs. cranial approach; c. Retroperitoneal approach vs. cranial approach; a–c for laparoscopic surgery and robotic surgery, respectively)
2. Short-term results of robot-assisted and laparoscopic surgery (Comparison in all approaches, medial approach, retroperitoneal approach, and in each ASA-PS, respectively)
3. Short-term results by degree of lymph node dissection (D2, D3v, D3a)
4. Long-term results by approach, robot or laparoscopy, and degree of dissection
5. Impact of experience on short-term and long-term outcomes after the surgery performed by the surgeons before obtaining board certification in gastrointestinal surgery (including the investigation by each approach, robot/laparoscopy, and degree of lymph node dissection)
6. Impact of surgeons’ case volume prior to obtaining board certification in gastrointestinal surgery on short- and long-term outcomes following robot-assisted procedures
7. Impact of the participation of Endoscopic Surgical Skill Qualification-certified surgeons in surgery and their role in the procedure on short- and long-term outcomes
8. Impact of anastomosis method on short- and long-term outcomes
9. Relationship between the presence of drain insertion and incidence and severity of complications
10. Risk factors for intestinal obstruction (long- and short-term)
11. Risk factors for complications and severity of complications in older adults

*ASA-PS* American Society of Anesthesiologists physical status

### Observation, investigation data, and methods

Data will be obtained from the participants’ medical records. All data to be obtained are used in daily medical care, and their frequency is equivalent to it. The principal investigator or co-investigator at each site is responsible for registering cases and entering medical data into the Electronic Data Capture system. Recording by a medical assistant is also permitted, provided it is approved by the principal investigator or co-investigator.

Participating institution backgroundInstitution type and sizePatient backgroundPatient age; sex; body mass index; American Society of Anesthesiologists Physical Status; Eastern Cooperative Oncology Group performance status; albumin level; lymphocyte count; presence of dementia, diabetes, chronic kidney disease, chronic liver disease, or respiratory comorbidities; history of cardiac or cerebrovascular disease; use of steroids/immunomodulators and antithrombotic drugs; preoperative bowel obstruction; preoperative anaemia; abscess or peritonitis; preoperative therapy; history of laparotomy; timing of surgery; primary tumour location; and tumour stage at initial diagnosis (clinical stage, T factor, N factor).Technique and surgeonsWhether the surgeon is a board-certified gastrointestinal surgeon, whether an Endoscopic Surgical Skill Qualification-certified surgeon participates in the operation and his or her role, the approach, blood vessels to be dissected, procedure of dissecting the accessory right colic vein (via the cranial or caudal side), level and direction of lymph node dissection, instruments used during node dissection, method of anastomosis, combined resection of other organs, whether a robot is used, number of previous robotic-assisted right-sided colon resections (ileal resection, right hemicolectomy, or extended right hemicolectomy), and whether a robotic surgery proctor participates in the surgery if robotic surgery is used.Surgical outcomesThe date of surgery, operation time, blood loss, presence of intraoperative vascular injury, other intraoperative complications, 30-day postoperative survival, open conversion, intraoperative blood transfusion, details and grade of postoperative complications within 30 days (Clavien–Dindo classification grade ≥ II), onset and date of intervention for cases with anastomotic leakage/deep wound infection (surgical site infection [SSI]), enforcement and date of reoperation, drain placement, anti-adhesive placement, date of discharge, and operative death.In cases of intraoperative vascular injury:Timing of intraoperative vascular injury; response to intraoperative vascular injury; unplanned bowel resection due to bleeding; open conversion due to bleeding; final post-haemostatic status; and amount of blood transfusion, blood products, and albumin administered from intraoperative to postoperative day 3.Surgical deathsCause of death, date of death, and date of therapeutic intervention.Pathological and histological findings and postoperative courseTumour diameter, histological type (main), pathological stage, T-factor, N-factor, R-status, number of harvested lymph nodes, number of lymph node metastases, presence and details of adjuvant therapy, survival outcome, date of confirmation of final survival outcome, date of confirmation of recurrence, and type of initial recurrence.Patients with pStage 0 and pStage IV will be censored, and no follow-up will be performed after initial postoperative discharge. The development of intestinal obstruction (Clavien–Dindo classification grade ≥ II) and abdominal wall scar hernia will be investigated during follow-up. Patients will be followed up during the postoperative period according to the Japanese Society for Cancer of the Colon and Rectum guideline schedule, and tumour marker levels, thoracoabdominal computed tomography (CT) results, and colonoscopy results will be collected. Omitting observations as part of routine medical care will be deemed acceptable at the discretion of the treating physician [36].

### Definition of assessment data

Type of institution: distinguishes between university-affiliated hospitals or cancer centres, equivalent institutions, and others.Size of institution: number of laparoscopic right-sided colectomies (ileal resection, right hemicolectomy of the colon, or right hemicolectomy of the extended colon) for colorectal cancer per year (including robotic surgery).Definitions of the preoperative medical conditions are described in Table 2.

**Table 2 Tab2:** Definitions of preoperative medical conditions

ASA-PS	American Society of Anesthesiologists physical status classification as described in the anaesthesia record
ECOG-PS	Score 0–4 (https://jcog.jp/doctor/tool/ps/) 0: Able to perform activities without any problems. Can perform the same daily activities as before the onset of illness without limitations 1: Physically able to walk and perform light or sedentary tasks, although physically strenuous activities are limited 2: Able to walk and perform all personal activities but not work. Spends > 50% of the day out of bed 3: Able to perform limited personal activities. Spends > 50% of the day in bed or chair 4: Unable to move at all. Unable to perform any personal activities. Spends all day in bed or chair
Dementia	Case officially diagnosed by a psychiatrist
Diabetes	On oral or insulin therapy. Or untreated and HbA1c level above the institutional norm. If HbA1c level is ≥ 8.0 or higher or equivalent within 2 weeks before surgery, it is considered poorly controlled
Chronic kidney disease	eGFR < 40. Classified as with/without dialysis
Cardiac disease	A history of myocardial infarction or angina, or heart failure presenting with fatigue, dyspnoea, or anginal symptoms during routine physical activity (equivalent to NYHA class II or higher), or more severe manifestations, is noted. Other cardiac conditions include moderate or greater aortic stenosis, arrhythmias excluding sporadic extrasystoles, post-pacemaker or ICD implantation, pulmonary hypertension, and cardiac sarcoidosis. Cases of unstable angina, myocardial infarction occurring within 7–30 days of onset, left ventricular ejection fraction (LVEF) < 40% or equivalent, and severe aortic stenosis are specifically categorised as high-risk
Cerebrovascular disease	Cerebrovascular disease will be categorised as follows: - History of cerebrovascular events with minimal or no residual deficits, including transient ischaemic attack (TIA) - Untreated cerebrovascular stenosis - Cerebrovascular disease with persistent neurological sequelae
Respiratory comorbidity	Patients with dyspnoea or more severe symptoms when walking uphill or on stairs (Hugh–Jones II equivalent). Cases on HOT therapy are included in the severe category
Asthma	Cases currently on medical therapy. This will be classified as inadequate/poorly controlled if symptomatic or with decreased forced expiratory volume% in 1 s within 1 month before surgery, or equivalent
Steroid/immunomodulator usage	Any type and dose being used at the time of initial diagnosis
Chronic liver disease	Child–Pugh B or higher, to be distinguished from Child–Pugh C
Antithrombotic drugs	Classified as none, on medication, or withdrawal. Any type of drug. If more than one drug is taken on the day of surgery, the patient is considered to be on medication

*ASA-PS* American Society of Anesthesiologists physical status, *ECOG-PS* Eastern Cooperative Oncology Group performance status, *HbA1c* glycated haemoglobin, *HOT* home oxygen therapy, *NYHA* New York Heart Association, *ICD* implantable cardioverter defibrillator, *LVEF* left ventricular ejection fraction, *TIA* transient ischaemic attack

(4)Preoperative bowel obstruction: requires intervention, such as quasi-emergency surgery, emergency surgery, preoperative gastrointestinal tube insertion, preoperative stent insertion, or stoma creation.(5)Preoperative therapy: at least one preoperative administration of anticancer or other drugs.(6)Laparotomy history: history of open or laparoscopic appendectomy or transabdominal preperitoneal (TAPP) hernia repair, procedures other than open or laparoscopic appendectomy or TAPP hernia repair, or none.(7)Timing of surgery: classified as routine, semi-urgent (performed within 1 week of the initial visit or with an earlier surgical schedule between routine and urgent), or urgent (first visit or the day after; the day of or after the onset of perforation, obstruction, bloody bowel discharge, etc.).(8)Primary tumour site: according to the Japanese Classification of Colorectal, Appendiceal, and Anal Carcinomas [37].(9)Stage at initial diagnosis: T and N staging according to the Japanese Classification of Colorectal, Appendiceal, and Anal Carcinomas [37].(10) Board-certified gastrointestinal surgeon participation: Whether the surgeon is board-certified by the Japanese Society of Gastroenterological Surgery. A surgeon is classified as a complete, partial, or non-certified operator.(11) Robotic surgery proctor participation: in robotic surgery, participation of a proctor certified by the Japan Society for Endoscopic Surgery as a surgeon, assistant, or consultant for robotic colon or colorectal procedures.(12) Endoscopic Surgical Skill Qualification System (ESSQS)-certified surgeon participation: whether an ESSQS-certified surgeon (certified by the Japan Society for Endoscopic Surgery) participates as a surgeon, assistant, scope operator, consultant, or partial participant (either as a partial surgeon, assistant, consultant, or scope operator).(13) Dissected vessels: Record whether the ileocecal artery, right colic artery, and the main trunk or branches of the middle colic artery are dissected. Also document whether accompanying veins are dissected and whether the anterior surface of the superior mesenteric artery (SMA) or superior mesenteric vein (SMV) is exposed.(14) Approaches: classified as medial, retroperitoneal, cranial, or other.

The definitions of these approaches were compiled using a previous survey on the details of each approach used in the attending institutions [see Additional file 1]. The description below covers the details of each approach used in the institutions that responded to the survey. Broadly speaking, the medial and cranial approaches are defined as procedures in which lymph node dissection precedes mesocolic mobilisation, whereas the retroperitoneal approach is defined as one in which mesocolic mobilisation precedes lymph node dissection.

Medial approach: dissection is initiated from the caudal side of the ileocecal artery, and lymph node dissection is performed prior to mesocolic mobilisation. The basic surgical procedure includes the following: (i) dissection of the ileocecal artery and vein from the retroperitoneum; (ii) lymph node dissection of the surgical trunk; (iii) dissection of the accessory right colonic vein; and (iv) mesocolic mobilisation by dissection of the cranial, caudal, and lateral attachments. This approach also includes cases in which cranial mobilisation, which creates a cranial termination point for lymph node dissection, is preceded by the standard procedure.

Retroperitoneal approach: mobilisation of the mesocolon from the retroperitoneum is initiated at its caudal origin, and lymph node dissection is performed after mesocolic mobilisation. The basic surgical procedure includes the following: (i) mobilisation of the mesocolon from the retroperitoneum initiated at its caudal origin (regardless of the degree of lateral mobilisation); (ii) lymph node dissection of the surgical trunk; and (iii) dissection of the accessory right colonic vein, opening of the omental bursa, or hepatic mobilisation. This approach also includes cases in which cranial mobilisation, which creates a cranial termination point for lymph node dissection, is preceded by standard lymph node dissection.

Cranial approach: dissection begins by opening the omental bursa and hepatic attachment, and lymph node dissection is performed prior to mesocolic mobilisation. The basic surgical procedure includes the following: (i) opening of the omental bursa, (ii) dissection of the right accessory colic vein or hepatic attachment, (iii) lymph node dissection along the surgical trunk, and (iv) mobilisation of the lateral/caudal attachments. Whether lymph node dissection is performed from the cranial to the caudal side or from the caudal to the cranial side does not matter.

(15) Robot usage: classified into da Vinci (except SP), Hinotori, Hugo, other models, or no usage.(16) Anastomosis method: classified into functional end-to-end anastomosis, overlapping anastomosis, delta anastomosis, and others. Additionally classified as intracorporeal or via a small laparotomy.(17) Methods for dissecting the right accessory colonic vein: dissection from the cranial and caudal sides.(18) Direction of lymph node dissection: the dissection procedure of the surgical trunk is classified into caudal to cranial, cranial to caudal, and caudal to cranial after setting a cranial termination point.(19) Lymph node dissection: classified as D0–1, D2, D3v, and D3a. The definitions are as follows.aFor the ileocecal and right colic arteryD2, the ileocecal or right colic artery is dissected proximally without SMV exposure; D3v, the anterior face of the SMV is exposed, and the ileocecal or right colic artery is dissected proximally; D3a, the anterior face of the SMA is additionally exposed, and the ileocecal or right colic artery is dissected at the root.bFor the middle colic arteryD2, the right/left branch of the middle colic artery (MCA) is dissected proximally. The main trunk of the MCA is not exposed; D3v, the main trunk of the MCA and anterior face of the SMV are exposed, and the right branch or trunk of the MCA is dissected proximally; D3a, the MCA main trunk and anterior face of the SMA are exposed, and the right branch or trunk of the MCA is dissected at the root.

The degree of dissection is judged based on the dissection of the dominant main vessel, regardless of SMV exposure during the procedure.

(20) Synchronous other-organ resection: description of synchronously resected organs: duodenum, jejunoileum, colon, liver, gallbladder, pancreas, iliopsoas muscle, inferior vena cava, aorta, iliac artery and vein, SMA and SMV, peritoneum of the abdominal wall adjacent to the colon, gonadal vessels, mesentery of other intestinal tracts, and others.(21) Devices used during lymph node dissection: monopolar, bipolar (including sealing devices), ultrasonic coagulation, and incision devices.(22) Intraoperative vascular injury: intraoperative injury to any of the following vascular organs: SMA, SMV, accessory right colonic vein, ileocecal artery, right colonic artery, MCA, anterior superior pancreaticoduodenal vein, right gastroduodenal vein, gastrocolic trunk, terminal ileal branch, first jejunal vein, and others (e.g., inferior vena cava).

Injury is classified as:

(i) Haemostasis achieved by compression, application of a haemostatic agent, and cauterisation (including soft coagulation with suction), with the injured vessel preserved without transection; (ii) haemostasis with sutures (including the final addition of sutures after temporal haemostasis) to preserve the injured vessels; (iii) ligature of the injured vessel, ligature/clip of the injured vessel (including those added after temporal haemostasis), and vessel dissection (including those dissected for lymph node dissection); (iv) haemostasis achieved by compression, application of a haemostatic agent, or cauterisation (including soft coagulation with suction) of the injured vessel; however, the vessel is later dissected for lymph node dissection (if unsure between iii and iv, select iii); and (v) details will be provided for other cases (e.g. the injured vessel is cut, but haemostasis is achieved only by cauterisation and left alone, or the vessel is dissected, and haemostasis is achieved using an ultrasonic coagulation incision device).

(23) Final bleeding control: possible/impossible (operative death).(24) Timing of intraoperative vascular injury: during lymph node dissection, mobilisation, intracorporeal anastomosis, extracorporeal anastomosis, and others (described at the time of adhesion dissection, drain insertion, etc.).(25) Other intraoperative complications: list those requiring intraoperative intervention (e.g., injury to other organs).(26) Open conversion: a skin incision ≥ 8 cm is generally defined as an open conversion. However, if the incision exceeds 8 cm solely for the purpose of tumor extraction, it shall not be considered an open conversion.(27) Postoperative complications (within 30 days): Clavien–Dindo classification grade ≥ II should be used.(28) Date of onset of anastomotic leakage/deep SSI: the date of onset is defined as the earliest time of abnormality during the initial physical examination, such as fever, abdominal pain, abnormal discharge from the drainage tube, blood test, and imaging.(29) Treatment intervention date: the date of treatment intervention is defined as the date corresponding to any of the following: administration of medical therapy (in the case of Clavien–Dindo classification grade II); performance of endoscopic, surgical, or interventional radiology (IVR) procedures without general anesthesia (grade IIIa); performance of endoscopic, surgical, or IVR procedures with general anesthesia (grade IIIb); or admission to the intensive care unit (ICU) (grade IV). Additionally, in cases of anastomotic leakage or deep surgical site infection (SSI), the date should be recorded if a new percutaneous drain is inserted or an existing one is replaced.(30) 30-day death: death from any cause within 30 days of surgery.(31) Surgical death: 30-day death or death during hospitalisation 31–90 days postoperatively.(32) Histological type, pathological stage, T and N stages, and R status: according to the Japanese Classification of Colorectal, Appendiceal, and Anal Carcinoma, third English Edition [37].(33) Postoperative adjuvant therapy: indicate whether at least one course has been completed, and specify the type of chemotherapy administered.(34) Recurrence-free survival: duration from the date of first treatment (surgery or start of preoperative therapy) to the date of the last confirmed recurrence-free/recurrence.(35) Local recurrence: local recurrence will be assessed based solely on the initial recurrence, with distinctions made between lymph node recurrence, anastomotic site recurrence, and other locations.(36) Intestinal obstruction during follow-up (Clavien–Dindo classification grade ≥ II): only the first occurrence 30 days after surgery will be considered.(37) Abdominal wall scar hernia: this will be diagnosed based on imaging findings, such as CT, or palpation of the hernia in the surgical scar. Only the first occurrence 30 days after surgery will be considered.

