### Statistical analysis

The analysis of primary endpoints, key secondary endpoints, and other secondary endpoints regarding short-term outcomes will begin as soon as 120 days after the patient enrolment period ends. Long-term outcome analysis of the secondary endpoint shall be performed upon completion of the 5-year follow-up period for all enrolled subjects.

Primary/key secondary endpoints: Summary statistics of patient background and surgical outcomes will be calculated, and the proportion of major complications and intraoperative vascular injury around the SMV and their causes will be summarised. Logistic regression analysis will be performed using the factors listed in the survey items that may influence the rate of major complications and intraoperative vascular injury around the SMV. A random-effects model will be used to account for the differences between institutions. Patients who underwent open conversion before the lymph node dissection will be excluded from the analysis of key secondary endpoints, and the relationship between the extent and location of the damaged vessel and the magnitude of the effect on the perioperative period will be considered.

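### Operator certification and skill-qualified participation are not tied to the assignment at the start of the operation, so a takeover or call for help after a vascular injury can change the exposure class

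*Protocol article*

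**What the plan says.** All references are to the protocol article.

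- **Definition of assessment data, item 10** (board certification): "A surgeon is classified as a complete, partial, or non-certified operator". No time point and no handover rule is given.
- **Same section, item 12** (ESSQS): the item records whether a certified surgeon "participates as a surgeon, assistant, scope operator, consultant, or partial participant (either as a partial surgeon, assistant, consultant, or scope operator"). Planned presence and being called in share the same codes.
- **Observation, investigation data, and methods**: for injured cases the list opens with "Timing of intraoperative vascular injury; response to intraoperative vascular injury". It goes on to unplanned bowel resection, conversion, final haemostatic status and blood products.
- **Definition of assessment data, item 24**: timing means the surgical phase, "Timing of intraoperative vascular injury: during lymph node dissection, mobilisation, intracorporeal anastomosis, extracorporeal anastomosis, and others". Item 22 grades the injury by how haemostasis was obtained. Neither identifies who was operating.
- **Endpoints, Table 1**: item 5 is "Impact of experience on short-term and long-term outcomes after the surgery performed by the surgeons before obtaining board certification in gastrointestinal surgery". Item 7 is "Impact of the participation of Endoscopic Surgical Skill Qualification-certified surgeons in surgery and their role in the procedure on short- and long-term outcomes". How the partial class is grouped is not stated.
- **Statistical analysis**: "Logistic regression analysis will be performed using the factors listed in the survey items that may influence the rate of major complications", and likewise for vascular injury around the superior mesenteric vein, with a random effect for institution. Operator status and ESSQS participation are among the survey items, so both are candidate factors.

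**The concern.** An exposure should be fixed before the outcome can act on it. Take an operation begun by a non-certified surgeon. Without an injury it stays *non-certified*. With an injury that brings a certified surgeon to the table, it can be coded *partial*. In the same way, a case planned without an ESSQS-certified surgeon becomes a case with ESSQS participation once one is called in to help with bleeding. The outcome then helps to decide the exposure.

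The effect would be to thin injuries out of the pure non-certified and no-ESSQS classes and to concentrate them in the partial, consultant and called-in classes. ESSQS involvement could look harmful, and surgery wholly in non-certified hands could look safer than it is. The Background names the role of surgeon proficiency and of ESSQS participation among the questions the data collection should address, so these coefficients will be read. A random effect for institution and propensity matching on baseline factors adjust for what precedes the operation. They cannot remove a reclassification caused by the outcome itself.

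**Working it through.** The article states no figure on this point, so there is none to reproduce. The check is an expected-count illustration.

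**Inputs**
- True injury rate r = 3% in every group (Background, the rate given for D3 dissection).
- Target N = 2,000 (Target number of cases).
- Assumed, because the article gives none of them: share of cases begun by non-certified surgeons s = 30%; probability of takeover after an injury t = 30%, 50% or 70%; probability of takeover without an injury u = 10%.

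**Formulas**
- Injury rate in *non-certified* = r(1−t) / [r(1−t) + (1−r)(1−u)]
- Injury rate in *partial* = rt / [rt + (1−r)u]
- Odds ratio, *non-certified* versus *complete* = (1−t)/(1−u), against a true 1.00
- Odds ratio, *non-certified* versus *complete* and *partial* pooled = [(1−t)/(1−u)] × [(1−s)+su] / [(1−s)+st]

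**Worked case, t = 50%.** 30% of 2,000 is 600 cases begun by non-certified surgeons: 18 with an injury, 582 without. Takeover moves 9 injured and 58.2 uninjured cases. *Non-certified* keeps 9/(9 + 523.8) = 1.7%. *Partial* shows 9/(9 + 58.2) = 13.4%. The odds ratio is 0.5/0.9 = 0.56.

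| t | Non-certified | Partial | Complete | OR, non-certified vs complete | OR, non-certified vs complete + partial |
|---|---|---|---|---|---|
| 30% | 2.3% | 8.5% | 3.0% | 0.78 | 0.72 |
| 50% | 1.7% | 13.4% | 3.0% | 0.56 | 0.48 |
| 70% | 1.0% | 17.8% | 3.0% | 0.33 | 0.27 |

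**ESSQS participation.** If item 12 is read as any participation versus none, the last column applies, with s now the assumed share of cases begun without an ESSQS-certified surgeon. Inverted, participation shows odds ratios of 1/0.719 = 1.39, 1/0.477 = 2.10 and 1/0.267 = 3.74 when the truth is 1.00.

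**A real difference.** If the true rates are 4.5% (begun by non-certified) and 3.0%, the true odds ratio is (0.045/0.955)/(0.03/0.97) = 1.52. Multiplying by (1−t)/(1−u) gives 1.18, 0.85 and 0.51, so an excess could appear protective.

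**Cases without bias.** If t = u, every odds ratio above that starts from 1.00 stays at 1.00. If *partial* is pooled with *non-certified*, and every partial case was begun by a non-certified surgeon, the rates are 3.0% and 3.0%.

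**Postoperative complications as the outcome.** Assume 8% complications without an injury and 24% with one, takeover acting only through the injury. The rate in a class is 8% + 16% × its injury rate. *Complete*: 8 + 16 × 0.030 = 8.48%. *Non-certified*: 8.38%, 8.27% and 8.16% for the three values of t. *Partial*: 9.4%, 10.1% and 10.8%. The shift for non-certified is 0.10 to 0.32 percentage points.

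**After the fix.** Classed by starting operator, the group begun by non-certified surgeons returns to 3.0% and the odds ratio to 1.00 for every t and u tried.

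**The case against.** The strongest reply has five parts.

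1. A reader might infer that the article classifies by who ended up operating. It does not say so. Items 10 and 12 are silent on timing, and item 12 records role, not share performed. This stands: the defect is a missing anchor, not a wrong one.
2. A reader might also infer that injuries are moved out of the trainee group and into the certified group. The partial class keeps such cases visible, and Table 1 item 5 does not say how that class is grouped. Pooling it with non-certified is open to the analyst. This stands in part: planned sharing begun by a certified surgeon would be pooled too, and the listed fields cannot identify it. For item 12 no such pooling separates planned from rescue participation.
3. The Statistical analysis section makes grade ≥ II complications the main short-term endpoint for the subgroup comparisons. The large distortion belongs to vascular injury, not to that endpoint. This stands, and the working shows the difference in scale.
4. The Background question of which technique is safest for young surgeons compares techniques within their cases. If takeover is equally likely under each technique, that odds ratio is unchanged. This stands.
5. The article condenses a fuller protocol, and the data capture form is not shown, so a field for handover may exist. If it does, only the definitions and the analysis class need amending. The definitions are printed here and lack the anchor either way.

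**Conclusion.** The concern holds in a limited form. As written, items 10 and 12 allow an injury to alter the operator or ESSQS class, and the listed fields do not let the analyst tell planned sharing from rescue. The consequence is confined mainly to the operator and ESSQS coefficients in the vascular-injury logistic model and to vascular injury as an outcome under Table 1 items 5 and 7. It is clearest for item 12.

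On the assumed takeover rates (30% to 70% after injury, 10% otherwise), a null odds ratio for non-certified versus complete would be reported as 0.78 to 0.33. The size rests wholly on how much likelier takeover is after an injury, which the article does not quantify; at equal rates it is nil. For complications the shift is a few tenths of a percentage point at most under the assumptions shown. The overall rates of severe complications and of vascular injury in all patients do not depend on these classes and are unaffected. The article does not support the conclusion that surgery by non-certified operators will necessarily look falsely safe.

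**What to change.** - In items 10 and 12, define operator status and ESSQS role by the planned or starting assignment. Use that class in the logistic models for the primary and key secondary endpoints and in Table 1 items 5 and 7.
- Add data capture fields for the reason for any handover or unplanned call-in (planned teaching split, difficulty, bleeding or injury) and for the operator's certification status at the moment of injury.
- Report unplanned takeover as an outcome, not as an exposure class.
- State how the partial class is handled. Where the starting assignment cannot be established, report a sensitivity analysis that pools partial with non-certified.

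**Cost.** A sentence in each item and a few fields. The real burden is retrospective: enrolment runs from 3 July 2024 to 31 May 2026, about 23 months, and the article appeared on 29 November 2025, about 17 months in. Cases enrolled by then must be completed from operative records with the outcome already known, so some entries will be missing or unclear. The number completed retrospectively should be reported.
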